**2.4 Blinding:**

This study will be double blinded. The placebo medication will be identical in taste and appearance to the itraconazole. Study drugs and placebo will be prepared by the central study pharmacy at the Ottawa Hospital and shipped to participating centres for distribution by the local research pharmacist according to randomization assignment.

**2.5 Patient Selection:**

A higher yield of fungal positive cultures is achieved with use of specific mycological culture media rather than with standard bacteriologic media in the clinical laboratory setting46. Therefore we will ask the microbiology laboratories at the hospital sites that participate in our study to routinely use mycologic media for all CF sputum cultures beginning 6-12 months before the start of the trial in order to identify a maximum number of patients with chronic aspergillus infection who will be potentially eligible.

**Inclusion Criteria*:***

- Diagnosis of CF as defined by two or more clinical features of CF and a documented sweat chloride > 60 mEq/L by quantitative pilocarpine iontophoresis test or a genotype showing two well characterized disease causing mutations
- Patient must be known to be chronically colonized with *Aspergillus fumigatus* (at least 2 sputum cultures within the last 12 months which have grown *Aspergillus fumigatus*, one of which must have been obtained within 4 months of randomization).
- Patients must be clinically stable at randomization according to the investigator. In addition, clinical stability will be defined as no use of **new** inhaled, oral or intravenous antibiotics or oral or intravenous corticosteroids during the 14-day period prior to randomization.
- 6 years of age and older at randomization
- Patients must weigh at least 20 kg at the time of randomization
- Patient must be able to perform lung function testing.
- Post-menarche females must be using an effective form of contraception.

**Exclusion criteria:**

- Inability to give informed consent.
- Respiratory culture positive for *B. cepacia* complex within one year of randomization
- Renal function abnormalities - Creatinine > 1.5 times normal within a 30 day period prior to randomization
- Liver function abnormalities - AST or ALT ≥ 2.5 times the upper limit of normal within a 30 day period prior to randomization
- Neutropenia , absolute neutrophil count ≤ 1000 within a 30 day period prior to randomization
- History of biliary cirrhosis or portal hypertension.
- Investigational drug use within 30 days of randomization date.
- History of alcohol, illicit drug or medication abuse within 1 year of screening
- History of lung transplantation or currently on lung transplant list
- Positive serum pregnancy test at screening (to be performed on all post-menarche females)
- Current treatment or previous history of treatment, with oral or intravenous antifungal agents within the last 12 months
- Pregnant or breastfeeding

Itraconazole can potentially interact with the following drugs- patients taking any of these drugs will be excluded from entering the trial: Immunosuppressives: Cyclosporine or Tacrolimus or Sirolimus, Antihistamines: Astemizole or Terfenadine, Hypnotics: Midazolam or Triazolam or Alprazolam, Cisapride , Pimozide, Quinidine, Statins: Atorvastatin, Lovostatin, Simvastatin, Tadalafil, Eletriptan, almotriptan, Vardenafil, Ergot derivatives, HIV antiretroviral agents: Didanosine, Nevirapine, Ritonavir, Indinavir.

**2.6 Proposed duration of the double blind treatment period:** Twenty-four weeks.

*Rationale for duration of treatment:*

Previous trials studying chronic antibiotic therapy for cystic fibrosis, such as the trials of inhaled tobramycin (TOBI) and trials of oral azithromycin therapy, have traditionally been of 24-weeks duration. These studies have been able to demonstrate significant biologic and clinical effects after 24 weeks of chronic antibiotic therapy, and chronic use of these therapies have become standard of care based on these trial results. Based on previous clinical studies we would expect eradication of fungal infection, or at least suppression of growth and a reduction of fungal burden, within several months of beginning therapy with itraconazole. In this context, a treatment period of 24 weeks with itraconazole should show a significant microbiological effect and an effect on pulmonary exacerbations and lung function. A 24-week period is also necessary in order to accumulate enough pulmonary exacerbation events to be able to show a difference between the two treatment groups.

**2.7 Study Period, frequency and duration of follow-up:** The multi-centre study will recruit patients over a period of 18 months and follow each recruited patient for a total of 48 weeks after they are randomized. Patients will be followed for 24 weeks while on study therapy and for an additional 24 weeks after study therapy has been discontinued. Primary outcomes for the study will be determined at 24 weeks, at the time point where the patient has just completed 24 weeks of active study therapy. However, we will follow patients for an additional 24 weeks after study therapy has been discontinued (ie. from weeks 24 to week 48 post-randomization) to determine if there are any lasting positive or negative carry-over effects of therapy with itraconazole. Efficacy and safety outcomes measured at 48 weeks will be assessed as secondary outcomes.

**2.8 Outcome Measures**

***Primary outcome measure:***  The primary outcome measure will be the proportion of patients who experience a respiratory exacerbation requiring intravenous antibiotics in the two treatment groups over the 24 week trial treatment period.

A pulmonary exacerbation will be defined according to clinical criteria published by the 1994 Cystic Fibrosis Foundation Microbiology and Infectious Disease Consensus Conference24. We have successfully used identical exacerbation criteria as an outcome in our previous multi-center CF clinical trial47. An exacerbation will be defined as the presence of at least three of the following 11 new findings or changes in clinical status when compared to the most recent baseline visit24:

- Increased cough
- Increased sputum production and/or change in appearance of expectorated sputum
- Fever (>38  C for at least four hours in a 24-hour period) on more than one occasion in the previous week
- Weight loss > 1 kg or 5% of body weight associated with anorexia and decreased dietary intake
- School or work absenteeism (due to illness) in the previous week
- Increased respiratory rate and/or work of breathing
- New finding on chest examination (eg. rales, wheezing, crackles)
- Decreased exercise tolerance
- Decrease in FEV1 of >10% from previous baseline study within past three months
- Decrease in hemoglobin saturation (as measured by oximetry) from baseline value within past three months of >10%
- New finding(s) on chest radiograph

An exacerbation must meet the above definition and it must also be associated with an acute change in regular CF medications, defined as physician-directed acute use of new intravenous antibiotics. The study will monitor patients for exacerbation via monthly telephone calls and via patient visits at 4, 12, 24, and 48 weeks after randomization.

CF pulmonary exacerbation was chosen as the primary outcome variable since it represents a well-defined clinical outcome that is understandable to patients and their physicians. Studies suggest that CF pulmonary exacerbations negatively affect health-related quality of life38. Furthermore, pulmonary exacerbations are associated with impaired sleep and neurocognitive abilities37 and with increased patient mortality39;40. This endpoint is also an important economic outcome, since those patients who have respiratory exacerbations generate higher health-care costs, both for physician visits, hospitalisations, and drug costs11;12.

We deliberately chose respiratory exacerbation requiring **intravenous antibiotics** as our primary outcome, rather than respiratory exacerbations requiring **oral or intravenous** antibiotics. The trial protocol will require patients to take oral itraconazole for 24 weeks and we did not feel that clinicians or patients would adopt this intervention in the future unless our clinical trial could show that the incidence of moderate and severe pulmonary exacerbations was reduced. Reduction of mild pulmonary exacerbations requiring brief courses of oral antibacterial antibiotics was not felt to be important enough to justify 24 weeks of therapy with itraconazole.

Adjudication of the primary outcome

For each suspected patient exacerbation a full report describing the circumstances of the suspected exacerbation will be prepared by study personnel. For every suspected exacerbation reported by the patient, we will obtain copies of the written medical record of the patient encounter. The assembled data from this visit will be presented to a blinded study Adjudication Committee for review.

**2.9 How will the outcome measures be measured at follow-up?**

***Secondary outcomes that will be assessed will include:***

1) The proportion of patients who experience a respiratory exacerbation requiring **intravenous** **or oral antibiotics** over the 24 week trial treatment period.

2) Absolute and relative changes in the forced expiratory volume in one second (FEV1) and forced vital capacity (FVC) over the 24-week treatment period.

3) Changes in disease-specific health-related quality of life over the 24 week study treatment

period as assessed by the CysticFibrosis Questionnaire (CFQ-R)- a disease-specific instrument that measures health-related quality of life for adolescents aged 14-18 and for adults with cysticfibrosis. The CFQ-R has been demonstrated in the European and American CF population to be reliable, valid, and responsive to change, and to correlate with SF-36 scores, pulmonary function, and disease severity. Scores are standardized on a 0 to 100 point scale with higher scores representing better quality of life. For children 6-14 years of age we will use the CysticFibrosis Children Questionnaire (CFQ-UK Children), a modified version of the CFQ-R that has been adapted and validated for use in the pediatric age group.

4) No. of exacerbations that result in hospitalisation over the 24-week treatment period.

5) Total number of hospitalisations (all cause) over the 24-week treatment period.

6) The mean number of exacerbations per patient over the 24 –week period.

7) The time to first exacerbation.

8) Premature discontinuation of study medication, for reasons of adverse effects or lack of

efficacy, as judged by the patient’s physician.

9) Incidence of adverse effects and serious adverse events.

10) Eradication of fungal infection/colonization. Those patients whose sputum is negative for fungal organisms on all 3 occasions at 24, 36 and 48 weeks after randomization will be considered to have had their sputum eradicated of fungus.

All efficacy and safety outcomes listed above will be assessed at 24 weeks, but also at 48 weeks after randomization, to determine if there are any lasting positive or negative carry-over effects of 24 weeks of therapy with itraconazole. Quality of life and pulmonary function will be measured at the time of randomization, and thereafter at 4, 12, 24, and 48 weeks after randomization.

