**2.10 Sample Size Calculations:**

The primary outcome measure will be the proportion of patients who experience a respiratory exacerbation requiring intravenous antibiotics in the two treatment groups over the 24 week trial observation period. In our combination antibiotic susceptibility trial we enrolled and followed 251 patients with cystic fibrosis and randomized patients when they experienced a pulmonary exacerbation. Eighty-seven patients (35%) experienced an exacerbation requiring intravenous antibiotics within 24 weeks of enrolment47. Similarly, 32% of placebo-treated patients in The Australian hypertonic saline trial experienced a CF exacerbation requiring intravenous antibiotics within 24 weeks48. Finally, in the TOBI study 100 of 258 actively-treated patients (39%), and 135 of 262 placebo-treated patients (52%) experienced at least one pulmonary exacerbation requiring intravenous antibiotics over the 24-week trial49.

Additionally, data from the 2005 Toronto CF Data Registry suggests that of Canadian adult and pediatric patients who are chronically infected with aspergillus, 27% experienced at least one respiratory exacerbation during the first six months of 2005 which required hospital admission and/or home intravenous antibiotic therapy. According to the statistician ([name]) who administers the database this is likely an under-estimation of the true rate of exacerbations, since data on hospitalizations or home IV therapy can be missing or incomplete within the database.

Thus, based on data from the above-mentioned three recently completed studies, and based on the Toronto database data, we conservatively expect that 34% of placebo-treated patients in our trial will experience a pulmonary exacerbation requiring intravenous antibiotics over the 24 week duration of our trial. The Trial Investigators (4 Canadian CF physicians and 4 Australian CF physicians) determined that a 15% absolute difference in 24-week exacerbation rates between the two treatment groups would be the minimal clinically significant difference that would be important for the study to detect.

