An MCID of 15% was decided upon for two reasons: 1) Data from Toronto suggests that at least 27% of pediatric and adult patients who are chronically infected with *A. fumigatus* experience a pulmonary exacerbation requiring IV antibiotics within a 24-week period, and that this risk is reduced to 11% in those who are not infected with Aspergillus (ie. a risk reduction of 16%). Thus a 15% absolute risk reduction might be expected if we can eliminate aspergillus infection in those study patients who are randomized to active anti-fungal treatment. 2) The study intervention is lengthy (24 weeks), expensive (approximately $16.00 per day for adults), and not without risk of side-effects. Therefore it was argued that unless a relatively large signal is seen, ie. unless the absolute risk reduction for exacerbation is at least 15%, then widespread implementation of the intervention would not be justified in the larger CF population. Assuming a binomial distribution for exacerbation rates, with a 15% absolute risk reduction between itraconazole vs. placebo, a two-sided alpha error of 0.05, and a beta error of 0.20, 148 patients per arm or 296 subjects in total are required. In order to allow for a 5% non-compliance rate (Lachin formula), a total sample size of 328 subjects is required.

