**2.14 Statistical Analysis**

*Principal Analysis of the Primary Outcome Measure:*

The final analysis will be performed with an ‘intention to treat’ approach. Patients will be included in the analysis according to the group to which they were randomized regardless of cross-over or compliance. Baseline characteristics of patients in the two treatment arms will be assessed using frequency distributions and univariate descriptive statistics including measures of central tendency and dispersion.

The principal analysis of the exacerbation proportions in the two treatment groups will be conducted using an unadjusted Fishers exact test comparing the proportion of events in the two treatment groups. A logistic regression procedure will be employed to adjust raw exacerbation proportions using important covariates that may be unbalanced at baseline that may influence outcomes (such as gender, baseline FEV1, home oxygen use, use of chronic inhaled antibiotics, use of chronic oral antibiotics, use of DNAse, use of hypertonic saline, and co-morbid illnesses).

We chose the proportion of patients having at least one exacerbation as a primary outcome measure rather than survival time to exacerbation. We believe that it is more clinically relevant to both patients and physicians to know whether or not a patient exacerbates rather than when they exacerbate. Therefore, an analysis of raw proportions followed by logistic regression procedures were chosen over log-rank tests followed by Cox proportional hazards modelling. Both alternative analytic approaches mentioned will be performed and reported.

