*Principal analysis of the secondary outcome measures:* All secondary outcome measures will be analyzed using an ‘intention to treat’ analysis. Any patients who drop out of the study before the 24 week mark will have measurements of airflow obstruction, dyspnea, and quality-of-life done on the last study visit carried forward for purposes of the analysis (ie. endpoint analysis, with the last observation carried forward). Continuous outcome measures including absolute and percent changes in FEV1 and changes in the scores of the components and the total score of the CysticFibrosis Questionnaire (CFQ-R) will be analysed using multi-variate repeated measures analysis of variance using the SAS Proc Mixed program. This procedure allows us to model the covariance structure of the data and allows for missing observations. Kaplan-Meier survival curves will be used to describe the probability of remaining exacerbation-free in the two treatment arms as a function of time from randomization into the study. The curves will be compared using the log-rank test statistic. Subsequently, Cox proportional hazards modeling will be performed to adjust for other variables that are unbalanced at baseline (such as gender, baseline FEV1, home oxygen use, use of chronic inhaled antibiotics, use of chronic oral antibiotics, use of DNAse, use of hypertonic saline, and co-morbid illnesses) that could potentially affect the time to next exacerbation. The mean number of exacerbations/patient will be calculated using a weighted approach to account for each patient’s duration of follow-up in the trial. The 95% confidence interval and the P value of the rate ratio will be obtained by using Poisson regression analysis models with log transformations of the number of exacerbations and the duration of follow-up.

***Other Considerations:*** P-values will be reported as two-sided. Data will be displayed as proportions and means with 95% confidence intervals or medians with interquartile ranges as appropriate. Likewise, measures of effect, odds ratios (logistic regression) and hazards ratio (Cox proportional hazards) will be presented with 95% confidence intervals.

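### Event outcomes assessed at 48 weeks to detect carry-over are not limited to events after week 24, so a comparison cumulative from randomisation would contain the on-treatment difference

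*Protocol*

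**What the plan says.** Section 2.9 lists ten secondary outcomes. Items 1, 4, 5 and 6 (proportion with an exacerbation treated by intravenous or oral antibiotics, exacerbations leading to hospitalisation, all-cause hospitalisations, mean exacerbations per patient) are defined over the 24-week treatment period. Items 7 to 9 (time to first exacerbation, premature discontinuation, adverse events) name no window. One sentence then extends the whole list: "All efficacy and safety outcomes listed above will be assessed at 24 weeks, but also at 48 weeks after randomization". Its stated purpose is to find out whether 24 weeks of itraconazole leaves an effect, good or bad, after it is stopped.

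Section 2.7 gives the same purpose, describes the additional follow-up as weeks 24 to 48, and adds: "Efficacy and safety outcomes measured at 48 weeks will be assessed as secondary outcomes". It does not define any event outcome on that window.

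Section 2.14 describes the exacerbation-free curves "as a function of time from randomization into the study. The curves will be compared using the log-rank test statistic", followed by Cox models, with no cut at week 24. The exacerbation rate is weighted by each patient's follow-up time in the trial. The principal comparison of exacerbation proportions "will be conducted using an unadjusted Fishers exact test comparing the proportion of events in the two treatment groups".

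**The concern.** The carry-over question concerns what happens once the drug is withdrawn. An event total at week 48 counted from randomisation has two parts: events on treatment (weeks 0 to 24) and events off treatment (weeks 24 to 48). Only the second bears on carry-over. If treatment works while it is taken and does nothing afterwards, the 48-week total still favours itraconazole, because the earlier difference stays in the count. The same applies in the other direction to cumulative adverse events.

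The stake is interpretation. Persistence after stopping is the stated reason for the second 24 weeks, and section 2.10 stresses that treatment is long, costly and not free of risk. A significant 48-week result could be reported as lasting benefit when it largely repeats the week-24 result.

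**Working it through.** **Inputs from the protocol (2.10 and 2.14)**
- Placebo 24-week risk 0.34: "we conservatively expect that 34% of placebo-treated patients in our trial will experience a pulmonary exacerbation requiring intravenous antibiotics over the 24 week duration".
- Reduction 0.15, hence 0.34 − 0.15 = 0.19 on itraconazole: "with a 15% absolute risk reduction between itraconazole vs. placebo, a two-sided alpha error of 0.05, and a beta error of 0.20".
- Size: "a two-sided alpha error of 0.05, and a beta error of 0.20, 148 patients per arm or 296 subjects in total are required"; then "In order to allow for a 5% non-compliance rate (Lachin formula), a total sample size of 328 subjects is required", that is 328/2 = 164 per arm.
- Test: Fisher's exact, taken here at two-sided 5%.

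**Assumption.** The protocol gives no risk for weeks 24 to 48. Call it q, equal in both arms (no carry-over) and independent of the first period. The base value is 0.34. The range is 0.27 (Toronto registry) to 0.52 (placebo arm of the inhaled tobramycin trial), both cited in 2.10.

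**The plan's own figure.** The two-proportion formula for 0.34 vs 0.19, 80% power and two-sided 5% gives 135 per arm. With continuity correction it gives 148, so 296 in total. Then 296/(1 − 0.05)² = 327.98, or 328. The sample size reproduces.

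**Cumulative 48-week risk** = 1 − (1 − risk at week 24)(1 − q).
- Placebo, q = 0.34: 1 − 0.66 × 0.66 = 0.564.
- Itraconazole, q = 0.34: 1 − 0.81 × 0.66 = 0.465.
- Difference: 0.15 × (1 − q) = 0.15 × 0.66 = 0.099, arising wholly in weeks 0 to 24.

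| q in both arms | Placebo, 0–48 | Itraconazole, 0–48 | Difference | Fisher significant, 148 / 164 per arm |
|---|---|---|---|---|
| 0.27 | 51.8% | 40.9% | 11.0 points | 44% / 48% |
| 0.34 | 56.4% | 46.5% | 9.9 points | 37% / 40% |
| 0.39 | 59.7% | 50.6% | 9.2 points | 32% / 35% |
| 0.52 | 68.3% | 61.1% | 7.2 points | 22% / 24% |

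The last column is by exact enumeration.

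**Same test confined to weeks 24 to 48, all patients, 34% in both arms:** significant in 3.8% of trials at either size.

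**Other event outcomes, q = 0.34.** Rates per 24 weeks are −ln(0.66) = 0.416 and −ln(0.81) = 0.211. Over 48 weeks the means are 2 × 0.416 = 0.83 and 0.416 + 0.211 = 0.63, a rate ratio of 0.75. A Poisson comparison is significant in 54% to 58% of trials. A log-rank test from randomisation carried to week 48 is significant in 56% to 61% (5,000 simulated trials per size).

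**If patients differ in underlying risk.** With gamma frailty of variance 0.5 to 2, the cumulative difference is 8.7 to 6.8 points. It is significant in 32% to 22% of trials at 148 per arm and 35% to 24% at 164 (normal approximation).

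**Would a weeks 24–48 hazard ratio for first exacerbation answer the question?** It compares only patients event-free at week 24. With gamma frailty of variance v and no carry-over, that ratio at week 24 is (0.81/0.66)^v: about 1.11 at v = 0.5, 1.23 at v = 1 and 1.51 at v = 2. It would suggest rebound harm where there is none.

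**The case against.** The strongest reply is that the protocol never orders a 0 to 48 week comparison for each event outcome. Four of them are defined over 24 weeks, and section 2.7 ties carry-over to weeks 24 to 48. Section 2.14 gives a time origin for the survival curves but no horizon. A statistical analysis plan, not shown here, could set the window correctly.

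Part of this stands. A reader might infer that the protocol mandates a cumulative carry-over test throughout; the text does not go that far. But it does more than leave a detail open. It attaches a stated purpose to an assessment at 48 weeks after randomisation, and the only time origin it gives is randomisation. The natural reading does not serve the purpose.

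A reader might also take the 22% to 48% as a false-positive rate for the trial. It is not. In the assumed scenario the 0 to 48 week difference is real, and it would be reported beside the 24-week result. The error lies only in calling it carry-over.

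Three limits on size also stand. The 164 per arm includes an allowance for non-compliance, so pairing it with the undiluted effect is favourable, and 148 is shown alongside. The later risk is assumed. The figures use the intravenous-only rate, whereas item 1 also counts oral treatment, for which the protocol gives no rate.

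**Conclusion.** The point holds as a matter of interpretation of secondary event outcomes. On the natural reading of 2.9, the 48-week comparison can suggest carry-over where none exists. With 34% vs 19% on treatment, equal later risk of 27% to 52%, independent periods and 148 to 164 per arm, the gap at week 48 is about 7 to 11 points. It is significant in about 22% to 48% of trials, against about 4% in the weeks 24 to 48 window. Allowing for frailty lowers the base-case figures but leaves them far above 5%.

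The documents do not support extending this to the 24-week primary outcome or the sample size. Nor does it apply to FEV1, FVC or quality of life, which are values measured at the week-48 visit, to fungal eradication, which has its own 24, 36 and 48 week definition, or to study-drug discontinuation, which cannot newly occur after week 24.

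**What to change.** In section 2.9:
- Define the carry-over comparison for exacerbations, hospitalisations and adverse events as events with onset in weeks 24 to 48, reported as the proportion with at least one and as a rate per person-time.
- Include all randomised patients still followed, whether or not they had an earlier event.
- Label any 0 to 48 week comparison as the overall effect of the treatment strategy.
- Censor time to first exacerbation at week 24 for the on-treatment effect, and do not use a weeks 24 to 48 hazard ratio for first event as the carry-over test.

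The cost is wording only; section 2.8 already plans exacerbation monitoring that includes a week-48 visit. The one downside is fewer events in the 24 to 48 week window, and so wider intervals there.
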